#### Body composition

Height will be measured. Weight, body mass index, skeletal muscle mass, and percentage of body fat will be obtained with bioelectrical impedance analysis (InBody 720; Biospace, Seoul, South Korea).

#### Physical measurement

The Abdominal test [36]: The subject lie down supine on a bench with knees flexed and heels about 0.30 m from buttocks. The arms have to be lifted with guided palms to level the knees so that the inferior angle of the scapula is barely lifted from the bench. The number of seconds that the position is maintained is recorded.

Measurement of upper body muscular strength: Handgrip strength is determined using digital dynamometer (TKK 5101 Grip-D; Takey, Tokyo, Japan). The precision will be 0.1 kg. For dynamometry measurement, patients maintain the standard bipedal position during the entire test with the arm in complete extension and they do not touch any part of the body with the dynamometer except the hand being measured. The determination of optimal grip span according to hand size is obtained through a simple algorithm which allowing the grip span to adapt to the hand size in women before the test [37]. Each subject will do three tests for each hand (alternating both hands) with 1 min of delay between measures. The final result will be the mean score for each hand. This test is valid and reliable [38].

Measurement of back muscle strength: Back muscle strength is assessed with a digital dynamometer (TKK 5002 Back-A; Takey, Tokyo, Japan). The precision will be 1 kg. The patients have to maintain a standing posture with 30° lumbar flexion [39]. Each subject will do three tests with 1 min of delay between measures. The mean from three tests is recorded.

Lower body endurance: Multiple sit-to-stand test is used to assess general lower extremity endurance [40]. Participants are asked, while sitting at the front of the chair, to rise until they reach full knee extension and sit back 10 times as fast as possible. The length of time taken to complete this will be recorded.This test has shown to be reliable [41].

### Cardiorespiratory fitness

The International Fitness Scale (IFIS) [42,43]: The IFIS is scored on a 5-point Likert scale with five response possibilities (‘very poor’, ‘poor’, ‘average’, ‘good’, and ‘very good’) and deals with perceived patients’ overall fitness, cardio-respiratory fitness, muscular fitness, speed-agility, and flexibility.

Functional capacity: The 6-min walk test using a treadmill (H-P-COSMOS for graphics; Germany) consists of determining the maximum distance (meters) that can be walked in 6 min. All participants have to be familiarized with the treadmill exercise protocol. Before the task participants are instructed to set their own pace, to ‘walk as far as you can in 6 minutes’ and to increase or decrease the speed of the treadmill voluntarily. During the task standardized phrases of encouragement are given. The examiner has to monitor the whole task because the participant must maintain a walking pace, defined as at least one foot being weight-bearing at all times. This test has shown to be reliable [44]. Before and after the task,heart rate, oxygen saturation, and Borg Fatigue Scale are controlled.

The International Physical Activity Questionnaire-Short Form (IPAQ-SF) [45]: This tool is used for cross-national monitoring of physical activity and inactivity. This self-administration version asks about three specific types of activity (walking, moderate-intensity activities, and vigorous-intensity activities) over the last 7 days.

### Fatigue

The Piper Fatigue Scale (PFS): The PFS is a validated tool to assess cancer-related fatigue. The PFS-revised (R-PFS) contains 22 items whose scores range from 0 to 10 and includes four dimensions of subjective fatigue: behavioral/severity, affective meaning, sensory, and cognitive/mood. The total fatigue score is calculated. The scale has high reliability (Cronbach’s α=0.96) [46].

The Borg Fatigue Scale [47]: The questionnaire presented a series of numbers arranged vertically from 6 (no perceived exertion) to 20 (maximum perceived exertion) as intensity of perceived exertion. It will be administered before and after carrying out the 6-min walk test.

### Anxiety and depression

The Hospital Anxiety and Depression Scale (HADS) [48,49]: This self-reporting tool assesses the possible presence of anxiety and depression in the setting of a medical non-psychiatric outpatient clinic. It contains 14 items (seven items for each subscale) with four-point Likert scale (ranging from 0 to 3). The global score ranges from 0 to 21 for anxiety and depression. The cutoff point for considering a pathological condition is 11 or above for both subscales.

### Cognitive function

The Trail Making Test (TMT) is one of the most important neuropsychological tests and provides information on speed for attention, sequencing, mental flexibility, visual search, and motor function [50]. The TMT consists of two parts. Part A requires the participant to draw lines to connect consecutive numbers (1 to 25) distributed on a sheet of paper as fast as possible. In part B, the participant must draw a consecutive line between numbers and letters (for example, 1-A-2-B-3-C, and so on). Before each part, a practical example is administered to ensure participants understand each part. When a mistake is made during the test, the examiner corrects it. Scoring is based on the length of time required to finish each part.

The Auditory Consonant Trigram (ACT) is also known as the Brown-Peterson procedure. This tool is used to test short-term memory, attention span, and information-processing capacity in adults [50]. The subject listens to the consonant trigram (CCC) at a rate of one letter per second following by a mental test as counting backward during delay intervals of 9, 18, and 36 s randomly. For the first five consonant trigrams, there is no delay interval (0 seconds) to recall the letters. Afterwards, the subject is asked to recall the trigram. Scoring is based on the total number of letters properly recalled in each delay interval.

### Accelerometry

The protocol for using and analysis of accelerometers has been published previously [51]. Participants will be asked to wear a tri-axial accelerometer (ActiGraph GT3X+, Pensacola, FL, US) over 8 consecutive days, starting the same day they receive the device. They will return the accelerometers to the researcher 9 days later. We will show them how to wear the accelerometer on their lower back with elastic belt all day (including sleeping hours). It is compulsory, for reasons of security, to take off accelerometers during aquatic activities (for example, bathing).

The first day of recording will not be included in the analysis, so a total of 7 days of recording (minimum of 10 h or more of registration per day) will be necessary to be included in the analysis. It will exclude from the analyses bouts of 60 continuous minutes of 0 activity intensity counts, considering these periods as non-wearing time. Monitor wearing time will be calculated by subtracting the non-wear time and the sleeping time (recorded with a diary of days/hours) from the total registered time for the entire day (typically 1,440 min). A recording of >20,000 counts per min will be considered as a potential malfunction of the accelerometer and the value will be excluded from the analyses.

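### The accelerometer inclusion rule demands 7 valid days out of 7, so one short day excludes a woman from that visit's analysis; two wear-time definitions also need tightening.

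*Protocol article*

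**What the plan says.** All of the rules stand in the Accelerometry section of the protocol article.

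- **Wear period.** The device is worn "over 8 consecutive days, starting the same day they receive the device", and "The first day of recording will not be included in the analysis".
- **Inclusion.** Of what is left, "a total of 7 days of recording (minimum of 10 h or more of registration per day) will be necessary" for a woman to enter the analysis. No smaller number of days is accepted anywhere in the article.
- **Night wear.** The device stays on "all day (including sleeping hours"), apart from aquatic activities.
- **Non-wear.** The analysis excludes "bouts of 60 continuous minutes of 0 activity intensity counts, considering these periods as non-wearing time". No exception is stated for the night.
- **Wear time.** It is obtained by "subtracting the non-wear time and the sleeping time" (the latter from a diary) from the day's total registered time, given as typically 1,440 min.
- **Source.** The section opens by pointing to a previously published accelerometer protocol, which is not part of the material at hand.

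The section on monitoring with accelerometers applies this to both groups at baseline, 8 weeks and 24 weeks. The Abstract lists accelerometry among the secondary outcomes. The Sample size section is built on overall quality of life, not on accelerometry.

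**The concern.** A rule that uses every available day has no slack. A device left off for one day, or one day with too few hours, costs all the data from that visit, including up to six good days.

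According to Randomization and blinding, the envelopes are opened after the baseline assessment, so exclusions at the two later visits happen after randomization. They depend on how well a woman wears the device. The telerehabilitation arm receives weekly session checks, calls and encouragement, whereas the control arm receives a written dossier, so compliance with the device could differ by arm. It could also go with activity level. Either would turn the accelerometry comparison into one between selected subsets.

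The second issue is definitional. The device is worn in bed, and an hour of zero counts is classed as non-wear. A still hour of sleep can therefore meet both definitions, and the article does not say what happens to the overlap. If such hours are removed twice, computed wear time is too low and any measure standardised to wear time has the wrong denominator.

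**Working it through.** **1. The rule itself.** Days worn 8, days dropped 1, days available 8 − 1 = 7. Days required 7. Spare days 7 − 7 = 0.

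**2. Retention per visit, independent days.** The article gives no daily compliance, so the probability p that a day is valid is an assumption, shown over a range. Share kept under 7 of 7 is p^7. Share kept under 4 of 7 is P(Bin(7, p) ≥ 4). The count applies p^7 to all 80 randomized women, before any other loss.

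| p (assumed) | 7 of 7 kept | of 80 women | 4 of 7 kept |
|---|---|---|---|
| 0.99 | 0.932 | 75 | over 0.999 |
| 0.98 | 0.868 | 69 | over 0.999 |
| 0.95 | 0.698 | 56 | over 0.999 |
| 0.90 | 0.478 | 38 | 0.997 |
| 0.85 | 0.321 | 26 | 0.988 |

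The Sample size section allows a maximum follow-up loss of 10%. That allowance was made for the quality-of-life outcome and serves here only as a yardstick. For the 7-of-7 rule alone to lose no more than 10%, p must be at least 0.90^(1/7) = 0.985.

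**3. Retention per visit, days correlated within a woman.** Use a beta-binomial with mean p and within-woman correlation ρ: s = (1 − ρ)/ρ, a = p·s, b = (1 − p)·s. The share with all 7 valid is B(a + 7, b)/B(a, b), where B is the beta function; the 4-of-7 share is the sum of the beta-binomial probabilities from 4 to 7.

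| p | ρ | 7 of 7 kept | 4 of 7 kept |
|---|---|---|---|
| 0.95 | 0.1 | 0.759 | 0.993 |
| 0.95 | 0.3 | 0.831 | 0.974 |
| 0.95 | 0.5 | 0.877 | 0.960 |
| 0.90 | 0.1 | 0.569 | 0.979 |
| 0.90 | 0.3 | 0.686 | 0.941 |
| 0.90 | 0.5 | 0.765 | 0.918 |

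Clustering helps the strict rule and slightly hurts the lenient one, so the gap narrows. At p = 0.90 it runs from 0.979 − 0.569 = 0.41 (ρ = 0.1) down to 0.918 − 0.765 = 0.15 (ρ = 0.5).

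**4. Wear time, two readings.** Assume 480 min of sleep, no true non-wear, and a share f of the sleep lying in zero-count runs of 60 min or more.

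- Overlap counted once: 1,440 − 480 = 960 min, whatever f is.
- Overlap counted twice: 1,440 − 480 − 480f. For f = 0, 0.25, 0.50, 0.75 and 1 this gives 960, 840, 720, 600 and 480 min.

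On the second reading, if the 10 h (600 min) refers to computed wear time, a fully worn day fails only when f exceeds 0.75. With 540 min of sleep, 60 min of true non-wear and f = 0.50, the result is 1,440 − 540 − 60 − 270 = 570 min, which also fails; counted once, that day has 840 min. If the 10 h refers to registered time before subtraction, neither day fails.

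**The case against.** **A full week is a defensible choice.** It gives every woman the same mix of weekdays and weekend. This stands as a reason to keep 7 of 7 as a sensitivity analysis. It does not justify discarding up to six good days in the main analysis.

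**The size of the loss is assumed.** This stands. At p = 0.99 only about 7% are lost per visit, and clustering reduces the larger losses. A reader might infer that the rule will discard many participants, or that it discards them selectively by arm. The article has no compliance figure and no data on exclusions by arm, fatigue or sleep, so neither can be asserted. Nor does it require a woman to be valid at all three visits, so multiplying retention across visits would go beyond the text.

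**Sleep is not said to be subtracted twice.** This also stands. A reader might infer a double subtraction from night wear combined with the zero-count rule. The text removes diary sleep once and non-wear once and is silent on the overlap. Setting diary sleep aside first fits the same sentence and produces no double count, and the published method to which the section refers may settle the order.

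**The 10 h may refer to registered time.** The section words the threshold as registration and uses registered time for the quantity before subtraction, so this reading is natural. On it, no overlap could fail a worn day, but the threshold would then barely test wear: a recording of typically 1,440 min passes almost automatically. The ambiguity matters either way.

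**Accelerometry is a secondary outcome.** Correct, and it limits the weight of the point.

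**Conclusion.** The point holds as a cheap improvement for a secondary outcome. The article states an inclusion rule with no tolerance: all 7 analysable days must reach 10 h. This is on the page and is not a detail left to another document.

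The cost depends on daily compliance, which the article does not give. With independent days the loss per visit is about 7%, 30% or 52% at p = 0.99, 0.95 or 0.90. With within-woman correlation of 0.1 to 0.5 it is about 12% to 24% at 0.95 and 23% to 43% at 0.90. Selection by arm or activity level is a plausible risk that the article does not demonstrate.

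On wear time, the finding is an ambiguity, not an established miscount: the formula permits an overlap between sleep and zero-count runs, and the time to which the 10 h applies is unclear. Nothing here touches the primary outcome or the sample size.

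**What to change.** 1. Accept a visit with a lower minimum of valid days, for example at least 4 including one weekend day, and analyse the daily mean over the valid days.
2. Keep 7 of 7 as a sensitivity analysis, and report the number of women excluded by arm and visit under each rule.
3. Remove diary sleep first and apply the 60-minute zero rule only to the remaining waking hours, so that no minute is subtracted twice. If the cited method already does this, one sentence saying so is enough.
4. State that the 10 h refers to waking wear time after these steps.

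The minimum of 4 is an example and comes from outside the article; whatever number is chosen should be fixed before the accelerometer data are analysed by group. The change needs no new data and no change to what participants do. Its cost is slightly noisier weekly means and a less uniform weekday and weekend mix for women with 4 to 6 valid days.

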### Lymphedema

Changes in size or volume of the upper limbs are measured to diagnose lymphedema. An inextensible flexible tape 0.5 cm wide × 2 m long with an accuracy of 0.1 cm will be used. According to research [52], the patient must be in an upright sitting position with both arms on a table, shoulders in neutral rotation and flexion of 45°, and forearms at maximum supination, the examiner will have to measure the circumference at 5-cm intervals along both arms, using the elbow fold as the reference beginning point. This procedure has been shown to be valid and reliable [53-55].

### Anthropometric perimeters

Perimeters of waist and hip: We will measure perimeters of waist and hip following the specific method [56]. An inextensible flexible tape 0.5 cm wide x 2 m long with an accuracy of 0.1 cm will be used. The examiner will measure the patient’s waist in a standing position placing the tape measure at the midpoint between the last rib and the upper anterior iliac spine. The measure will take place at the end of exhalation.

For the hip perimeter the patient will remain in a standing position and the examiner will place the tape measure at the midpoint between both trochanters to the level of maximum relief of the buttocks and symphysis pubis.

### Telerehabilitation group/intervention group

The intervention will be implemented by research group called CUIDATE. The e-CUIDATE system is an 8-week program (three training sessions per week) which aims to recover a healthy lifestyle in breast cancer survivors. Participants will have access to a range of exercises such as breathing exercises, mobility, strength, and stretching. All of these exercises will be assigned to women in the telerehabilitation group according to their perceived needs at baseline assessment. These needs will be established based on fatigue level, functional capacity (6-min walk test), and neck-shoulder pain reported by the patients. For this reason each participant will receive progressive personal training (for example, number and type of exercises, repetitions, series, and so on). We will instruct participants to use the telerehabilitation system on day 2 testing (username and password are provided for each participant). The participants’ aims will be set weekly; the CUIDATE group will then choose exercises aimed at achieving these goals. Furthermore women will receive telephone calls, text messages, and videoconference sessions (as required) to resolve any question or suggestion. Efforts will be made to prevent the telerehabilitation group receiving additional physical care.

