### Research design and methods

A randomized controlled trial will be conducted with assessments at baseline, 4 weeks and immediately after intervention (at 8 weeks). Follow-up measurements will be carried out 24 weeks after the end of the 8-week intervention period, giving a total trial data collection period of 32 weeks. The assessments will be performed on 2 separate days to avoid fatigue in the patients. The study assessment schedule is shown in Table 1.

**Table 1 T1:** Study assessment schedule

**Assessment**	**Baseline**	**Follow****-****up**	**Post****-****intervention**	**Detraining**
		**(4 weeks)**	**(8 weeks)**	**(24 weeks)**
Informed consent	X			
*Day 1 testing*				
Sociodemographic data	X			
Anthropometric data, pressure/rate heart	X		X	X
Training on the treadmill	X			
Lymphedema	X		X	X
*Day 2 testing*				
Piper Fatigue Scale-revised	X	X	X	X
Trail Making Test	X		X	X
Auditory Consonant Trigram	X		X	X
EORTC QLQ-C30	X	X	X	X
EORTC QLQ-BR23	X	X	X	X
International Fitness Scale	X		X	X
Brief Pain Inventory short form	X	X	X	X
Hospital Anxiety and Depression Scale	X		X	X
Visual Analogue Scale for pain	X		X	X
Algometry	X		X	X
Body composition	X		X	X
Handgrip strength	X		X	X
Back muscle strength	X		X	X
Multiple sit-to-stand test	X		X	X
Abdominal test	X		X	X
6-min walk test	X		X	X
Borg Fatigue Scale	X		X	X
Accelerometry (1 week)	X		X	X
*Questionnaire to be completed at home after accelerometry*				
Questionnaire	X		X	X
IPAQ-SF Satisfaction survey			X	

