### Follow-up at 8 weeks

Post-intervention assessment will be made to check on aims achievement. Support and encouragement will be given to follow with training sessions self-sufficiently because all participants will continue to have access to their profiles in e-CUIDATE.

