### Randomization and blinding

We allocated patients to a telerehabilitation program or control group in five randomization cycles, using computer-generated numbers (EPIDAT 3.1, Xunta de Galicia). The sequence was entered into numbered opaque envelopes by an external member and they were opened after completion of the baseline assessment. For ethical implications, those participants allocated to the control group, who finished the period of 6 months for the current study, were invited to receive the intervention when last outcome measurement was carried out. The researcher in charge of randomly assigning participants will not know in advance what treatment the next participant would receive and will not participate in assessment. Assessment staff will be blinded to the participant randomization assignment. No changes in assignment will be possible from the staff involved in the telerehabilitation program.

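### Log-in and system training are set for baseline day 2, but all analysed baseline accelerometry falls after day 2 and envelopes open only once baseline is complete; the order must be reconciled

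*Protocol article*

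**What the plan says.** Five statements in the protocol article bear on the order of events.

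- **Visits** (Research design and methods): "The assessments will be performed on 2 separate days to avoid fatigue in the patients".
- **Schedule** (Table 1, same section): the day 2 block includes "Accelerometry (1 week"), marked at baseline. Below it comes a block headed "Questionnaire to be completed at home after accelerometry", also with a baseline entry.
- **Wear period** (Accelerometry): the device is worn "over 8 consecutive days, starting the same day they receive the device". It goes back to the researcher 9 days later, and the first recorded day is left out of the analysis. Monitoring with accelerometers confirms that both arms are measured at baseline.
- **Access to the intervention** (Telerehabilitation group/intervention group): "We will instruct participants to use the telerehabilitation system on day 2 testing (username and password are provided for each participant").
- **Allocation** (Randomization and blinding): the envelopes are numbered and opaque, and "they were opened after completion of the baseline assessment". The same section states: "Assessment staff will be blinded to the participant randomization assignment".

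On the week-8 visit, Follow-up at 8 weeks says: "Post-intervention assessment will be made to check on aims achievement". It adds that participants are encouraged to keep training.

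**The concern.** A baseline is useful because it is taken before anyone knows the allocation and before the intervention can act. Here the arm-specific step (instruction plus a personal log-in) is tied to a testing day, while one baseline measurement only begins on that day and runs for the following week. The article does not say which comes first: the end of that week, the opening of the envelope, or the log-in.

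The outcomes at stake are accelerometry and probably IPAQ-SF, both secondary. If a woman knows she is in the exercise arm and has system access while her baseline activity is recorded, any early rise in activity is counted as baseline. An analysis that reads the effect as change from baseline then subtracts part of it. The reverse order, with instruction before allocation, would give system access to women who may later be controls.

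**Working it through.** No stated effect or power figure is involved, so the check is a day count followed by a comparison of the possible orders.

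**Day count.** Call baseline day 2 day 0. The article does not print the word baseline beside day 2 in the instruction sentence, but instruction given before an 8-week programme can only refer to that visit.

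| Event | Source | Day |
|---|---|---|
| Day 2 tests, device handed over, instruction and log-in | Table 1; Telerehabilitation group/intervention group | 0 |
| Device worn, 8 consecutive days | Accelerometry | 0 to 7 |
| First day dropped | Accelerometry | 0 |
| Analysed days | 8 − 1 = 7, matching the article's own 7 | 1 to 7 |
| Device returned | Accelerometry | 9 |
| At-home questionnaire | Table 1 | after the wear period |

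So 7 of 7 analysed baseline days lie after day 2, and the baseline as scheduled ends about 8 to 9 days after it. IPAQ-SF asks about the previous 7 days (Cardiorespiratory fitness), so if it is the at-home questionnaire, its recall covers the same week.

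**Possible orders.**

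1. *Envelope opened after the whole scheduled baseline.* Instruction and log-in on day 0 then come about 8 to 9 days before allocation. Women not yet allocated, future controls included, would be instructed, or the allocation would have to be known early.
2. *Envelope opened at the end of the day 2 clinic tests.* Instruction can follow allocation on the same day, but all 7 analysed accelerometry days are then recorded after the allocation is known and access has been given.

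Neither order gives both instruction after allocation and a baseline activity week before it.

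**Direction of the risk under order 2.** Let *e* be the between-arm difference in activity already present in the baseline week, and *d* the difference at week 8. A group × time contrast estimates *d* − *e* instead of *d*. If women become more active early, *e* has the same sign as *d* and the result moves toward no effect. If nothing changes until the device is returned, *e* = 0 and nothing is lost. The article gives no value for *e* and no date for the first session, so the ratio *e*/*d* cannot be calculated.

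**Which analysis is exposed.** Data analysis reports the group × time interaction, in which baseline is a time point. The ANCOVA covariates named there are age, stage, surgery type and time from diagnosis; the baseline value of the outcome is not among them. A week-8 comparison adjusted for those four alone would not be altered by a shifted baseline.

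**The case against.** The strongest defence is that baseline assessment, in the randomization section, means the two clinic days. The article does speak of 2 separate assessment days, and it describes accelerometry under its own heading as monitoring of habits. On that reading the envelope opens at the end of day 2, instruction follows, no control is trained, and every clinic test precedes allocation. This removes the conflict of order. It does not rescue the baseline activity week, because it is order 2 above. Nor does the article state this meaning, and Table 1 marks accelerometry as a baseline item.

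Several further objections stand and limit the point:

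- **Training during the baseline week is not shown.** A reader might infer that baseline activity is measured in the first intervention week. The article says only that women are instructed and given a log-in. Exercises are assigned individually from needs found at baseline, so sessions may begin later.
- **Not every participant's baseline is shown to be affected.** Under order 2 only the telerehabilitation arm, planned at 40 women, has access. Controls could be affected only through knowing their allocation.
- **IPAQ-SF is probable, not certain.** Its row in Table 1 is broken in the text available.
- **Assessor blinding is not shown to be broken.** A reader might infer this from instruction on a testing day and from the week-8 check on aims, since weekly aims are described only for the telerehabilitation arm. The article does not say that assessors do either task, and its wording is compatible with intervention staff doing both after the blinded tests.

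It is also fair to say that an article leaves much procedural detail to the full protocol. The point here, however, rests on what the article does state.

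**Conclusion.** The point holds as an inconsistency in the order of events with a limited reach. Taken together, the schedule, the wear period, the day 2 instruction and the envelope rule leave two options: instruction before allocation, or a baseline activity week recorded after allocation and access. The day count is firm for accelerometry (7 of 7 analysed days) and likely for IPAQ-SF.

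The consequence is a risk of bias toward no effect in the group × time result for those outcomes. It depends on order 2 being followed and on women becoming more active in that week. Its size is unknown, and any percentage loss would rest on an assumed early response. The primary QLQ-C30/BR23 baseline and the other clinic measures are unaffected provided envelope opening and instruction follow the day 2 tests. A change is worthwhile because it is cheap and protects a listed secondary outcome.

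**What to change.** Reconcile Table 1 and the sections on accelerometry, the intervention group and randomization so that they describe one order:

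1. Day 1 tests, then day 2 tests, with the device handed over on day 2.
2. Baseline is defined as complete when the accelerometer and the at-home questionnaire are returned.
3. The envelope is opened at that contact.
4. Only then do staff who take no part in assessment give instruction and log-in.

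The return contact already exists in the plan, so no procedure is added. The cost is that the intervention starts about 9 days later, and the clinic baseline is that much older when it does.

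As a secondary safeguard, state in Follow-up at 8 weeks that intervention staff carry out the aims review and encouragement, after the blinded tests are finished. This costs a sentence and makes explicit what the present wording leaves open.
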